### Intervention

Using Australian food composition data in addition to data on the AGE, N-carboxymethyllysine (CML), N-carboxyethyllysine (CEL), and methylglyoxal-derived hydroimidazolone (MGH1) content of common foods [3], a set of carefully matched alternative food choices has been designed with each alternate food choice having similar macronutrient and total energy content but differing greatly in AGE (referred to as the "Food List") [9].

To ascertain dietary AGE content, food items used in the study were obtained from local supermarkets and prepared according to the instructions of the study. To prevent neo-formation of CML during acid hydrolysis, a reduction step with sodium borohydride was used. Food items containing <20% fat were mixed and subsequently deproteinized with 1000 µl cold (4°C) TFA. Food items >20% fat were mixed and subsequently deproteinized with a mixture of chloroform:methanol (2:1, v/v) [22]. After centrifugation (4300 *g*, 4°C, 20 min), the supernatant (TFA) or lower phase (chloroform) was carefully removed. For validation experiments, 25 µL of a standard solution (six point calibration curve; 5250-0 nmol/L CML, 6250-0 nmol/L CEL and 14749-0 nmol/L MGH1) was added. Samples were then hydrolyzed by adding 500 µl 6N HCl and incubated for 16 hours at 100°C. After hydrolysis, 40 µL hydrolysate and 20 µL internal standard (containing 1432 nmol/L ^2^H2-CML, 1378 nmol/L ^2^H4-CEL, and 1322 nmol/L ^2^H3-MGH1) were mixed in a reaction vial. The mixture was evaporated to dryness under a stream of nitrogen gas at 70°C. To increase sensitivity during electrospray ionization and increase retention time using reversed phase chromatography, samples were subsequently derivatized with 100 µL 1-butanol:HCl (3:1, v/v) for 90 minutes at 70°C. After derivatisation, the samples were evaporated to dryness under nitrogen, redissolved in 300 µL water, mixed, and subsequently centrifuged at 20,000 *g* for 20 minutes. AGE-free adducts in foods were measured.

Using the 3-day diet diary recorded by each participant during the "run-in" period, the dietitian will help participants select foods for their first test diet from the "Food List", guided by their individual preferences and energy requirements. The content of their second test diet will comprise the alternate paired foods. Food choices on the high-AGE diet thus will approximate a typical Australian diet, while the isoenergetic low AGE diet, matched for macronutrient content, will have reduced AGE content through altered cooking techniques [23] and use of differently processed foods. All food required for both test diets will be provided weekly to the participants as ready-to-eat items or as packed food portions together with detailed instructions for storage and re-heating or cooking (method, temperature, duration). Participants will be asked to eat to appetite throughout both dietary periods to maintain constant body weight and to complete a daily record indicating the number of portions eaten for each food item supplied, any foods not consumed, or any additional foods that were eaten.

Participants will be contacted twice a week by the dietitian who designed the dietary protocol to resolve any problems and to ensure dietary compliance.

### Follow-Up Visits

Participants will be scheduled for their follow-up visits after completing each test diet for 2 weeks. All the procedures performed during baseline assessment including blood pressure, anthropometry, IVGTT, physical activity questionnaire, and glucose clamp will be repeated with the exception of the OGTT, as this will only be performed once at screening to identify undiagnosed diabetes.

### Safety Considerations

During the screening, baseline, and follow-up procedures, any medical conditions or abnormalities detected will be promptly discussed with the participant by a qualified medical practitioner involved in the study. Where applicable, participants will be treated, referred, and/or advised to visit their general practitioner for follow-up. All participants will be advised of the results of their medical review and blood tests after completion of the study, and a medical practitioner from the study team will provide them with strategies to improve their diabetes and cardiovascular risk profile.

### Ethics

This trial has received ethical approval from the Alfred Hospital Ethics Committee in Melbourne, Australia (Protocol ID: 36/06).

### Outcome Measurements

The primary outcome in this trial is the difference (change) in insulin sensitivity between the 2 diets. Secondary outcomes include changes in insulin secretion, body weight, body mass index (BMI), waist, waist-to-hip ratio (WHR), resting systolic and diastolic blood pressure, lipid profile and markers of inflammation (ie, interleukin (IL)-1ß, IL-6, IL-8, and IL-10), tumour necrosis factor-α (TNFα), macrophage migration inhibitory factor (MIF), monocyte chemotactic protein-1 (MCP-1), C-reactive protein (CRP), nuclear factor-κB (NF-κB) activity, and circulating sRAGEs.

### Data Collection and Analyses

#### Anthropometry

##### Body Mass Index (BMI) and Percent Body Fat

Body weight (kg) and height (cm) will be measured using a digital scale (BC-418MA, Tanita UK Ltd) and stable stadiometer (Seca 206), respectively, at baseline and following the intervention period during which participants will be lightly clothed and without shoes. BMI will be calculated as weight (kg)/height (m)^2^. Body composition will be determined by bioelectrical impedance analysis (BC-418MA, Tanita UK Ltd).

##### Waist-To-Hip Ratio (WHR)

Central adiposity will be assessed using waist and hip circumferences, taken in duplicate by an experienced researcher using a constant-tension tape. Waist circumference will be measured at the midpoint between the upper iliac crest and the lowermost rib at the end of a normal expiration, while hip circumference will be taken around the widest part of the buttocks. The WHR will be determined as waist (cm)/hip (cm).

#### Metabolic Measures

All metabolic testing will be performed after a 12-hour overnight fast. Prior to metabolic testing, participants will be asked to abstain from strenuous exercise and caffeine for 3 days. The first metabolic testing day in females will be scheduled in the follicular phase of their menstrual cycle.

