**Methods:**

Overweight, but otherwise healthy, non-diabetic adults (N=20) aged 18-50 years old will complete a randomized cross-over design intervention study alternating low and high (4-fold increase) AGE diets (2-week duration). At baseline, participants will undergo a medical review including an intravenous glucose tolerance test (IVGTT), a hyperinsulinemic-euglycemic clamp, and anthropometric measures and questionnaires assessing diet, physical activity, and general wellness. Each test diet will be followed for 14 days, followed by a 4-week washout period before commencement of the second alternate dietary period. Energy, macronutrient, and AGE intake will be calculated for each dietary period. Additionally, the AGE content of foods used in the study will be measured by ultra performance liquid chromatography mass spectrometry. All measurements will be repeated at the beginning and end of each dietary period. Primary and secondary outcomes will be expressed as a change over the dietary period for insulin sensitivity, secretion, anthropometric parameters, sRAGE, and inflammation markers and compared by paired *t* test and analysis of variance (ANOVA).

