## Methods

### Study Design and Setting

#### Overview

This study has a randomized, two period double-blind cross-over design (Figure 1). We aim for 20 overweight but otherwise healthy normoglycemic adults, aged 18-50 years to complete the trial. Participants will commence the study after a 2-week run-in on their habitual diet, but with restricted intake of alcohol, fast food, and coffee. Test diets will then each be followed for 2 weeks, separated by a 4-week washout period (return to habitual diet). Usual levels of physical activity will be continued throughout the study. Overweight participants will be selected for enrolment in this study as they represent the average Australian population, are generally more insulin resistant, more sedentary, and have higher levels of inflammatory markers, all factors that increase their risk for type 2 diabetes [17,18]. Participants will be sought using a number of advertising strategies including posters, flyers, newspaper, and online advertising and email newsletters from the Alfred Hospital in Melbourne, Australia.

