#### Exclusion Criteria

Exclusion criteria will include (1) substance abuse including smoking and high alcohol use (>4 and >2 standard drinks per week for males and females, respectively), (2) known allergies, (3) use of medications including vitamin supplements and hormonal contraceptives, (4) any renal, cardiovascular, hematological, respiratory, gastrointestinal, endocrine or central nervous system diseases, psychiatric disorders, active cancer within the preceding 5 years, or the presence of acute inflammation or infection based on the medical history and the physical and laboratory examinations obtained at recruitment, and (5) women in menopause, or pregnant and/or lactating.

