### Screening

The study timelines are presented in Figure 1. Female participants will be required to commence metabolic testing while they are in the follicular phase of their menstrual cycle and a urine pregnancy test will be performed to exclude pregnancy. At visit 1, screening will be undertaken by a registered medical practitioner who will collect the medical history and perform a physical examination including measurement of blood pressure, height, body weight, and waist and hip circumference using the methods outlined in the following sections.

At the second visit, participants will undergo an OGTT with measurement of fasting and 2-hour glucose levels to exclude diabetes according to the World Health Organization (WHO) 1999 criteria [20]. Blood samples will be analyzed by a single accredited laboratory for full blood count, kidney and liver function, lipid profile, and C-reactive protein (CRP) as a marker of inflammation. Participants will also be given a 3-day food diary to record their habitual dietary intake and this will be returned on their next visit where it will be used to aid the dietitian in the development of individualized test diets (as following).

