### Randomization and Blinding

Following successful screening and baseline assessment, subjects will be randomized by a computer program to commence the study with either the high or low AGE diet. Randomization will be done in blocks of four by gender using a relevant computer program to ensure balance in each test group and will be conducted by a researcher from within our department who is not involved in the trial data collection, analysis, or reporting. Diet type will be coded as (red or blue) by the dietitian, so that participants and blinded investigators remain unaware of which dietary period they are undertaking or how diet might affect glucose metabolism. Clinical and laboratory investigators will also be masked to diet allocation.

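### Only the first metabolic test is tied to menstrual phase, and matching tests lie 42 days apart, so many women's two diet periods fall in different phases and the unadjusted paired t test loses precision

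*Protocol article*

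**What the plan says.** Two places in the protocol article set a cycle-phase rule, and both concern only the start of testing. Screening: "Female participants will be required to commence metabolic testing while they are in the follicular phase of their menstrual cycle". Metabolic Measures: "The first metabolic testing day in females will be scheduled in the follicular phase of their menstrual cycle". No phase rule is stated for the end-of-diet tests or for the second period.

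The timing is fixed in the abstract, "Each test diet will be followed for 14 days, followed by a 4-week washout period before commencement of the second alternate dietary period", and again in the Overview. The abstract adds: "All measurements will be repeated at the beginning and end of each dietary period".

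The Exclusion Criteria remove "use of medications including vitamin supplements and hormonal contraceptives" and "women in menopause, or pregnant and/or lactating", so the women who enter are expected to have natural cycles. Under Randomization and Blinding: "Randomization will be done in blocks of four by gender".

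Outcome Measurements makes the between-diet difference in insulin sensitivity the primary outcome. The abstract expresses outcomes as changes over each diet period. Data Analysis compares the diets by paired t test. It places diet order in the multiple regression models and a diet-and-period interaction in an expanded model for carryover.

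**The concern.** The protocol treats cycle phase as worth standardising, yet standardises it on one occasion only. The primary outcome rests on clamps at the end of each diet and, for change scores, at the start as well.

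With a spacing of about one and a half cycles, a woman's matching tests in the two periods tend to fall in different phases. Any phase effect on insulin sensitivity then enters her between-diet difference, with a sign set by her diet order. In change scores it can enter twice. A paired t test has no period term, so this spread is counted as error. In women, a period effect also cannot be cleanly separated from phase.

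**Working it through.** **Calendar.** Diet starts are 14 + 28 = 42 days apart. Counting from the first diet start, tests fall on about days 0, 14, 42 and 56. The pre-diet tests (0 and 42) and the post-diet tests (14 and 56) are each 42 days apart.

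**Cycle shift.** The documents give no cycle length. Assume length L, with the luteal phase as the last 14 days. The shift between matching tests is s = 42 mod L. For a woman starting on any cycle day, the share of start days that put two matching tests in different phases is 2 × min(s, L − s)/L for the lengths below. The last column assumes the first pre-diet test falls on any follicular day.

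| L (days) | s | s/L | matching tests in different phases, any start day | luteal at day 42 after a follicular day 0 |
|---|---|---|---|---|
| 21 | 0 | 0.00 | 0% | 0% |
| 24 | 18 | 0.75 | 12/24 = 50% | 60% |
| 26 | 16 | 0.62 | 20/26 = 77% | 83% |
| 28 | 14 | 0.50 | 28/28 = 100% | 100% |
| 30 | 12 | 0.40 | 24/30 = 80% | 75% |
| 32 | 10 | 0.31 | 20/32 = 62% | 56% |
| 35 | 7 | 0.20 | 14/35 = 40% | 33% |

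The half-cycle shift at 28 days does not depend on which visit is the anchor. A common anchor only makes it run the same way in every woman. If day 0 is follicular and L = 28, the four tests are follicular, luteal, luteal, follicular.

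**Size of the term.** Let p be the luteal-minus-follicular difference in clamp values (not given; assumed 0.4 to 1.2 mg/kg/min, about 5% to 15% of 8.1). At 28 days a woman's between-diet difference gains ±p on end values. On change scores it gains ±2p, because her change is shifted by p in one period and by −p in the other. Write k for p or 2p.

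**Bias.** The shift in the mean is k × (women in one order − women in the other)/n. It is zero when women's orders are balanced. For a 6:4 split of 10 women among 20 completers and p = 10% of 8.1 = 0.81:
- end values: 0.81 × 2/20 = 0.08 mg/kg/min
- change scores: 1.62 × 2/20 = 0.16 mg/kg/min

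**Reference power.** The plan's difference is 0.20 × 8.1 = 1.62. With the stated SD of 1.0, a two-sided paired t test needs 6 people for 80% power, so the planned 20 is not reproduced. That is a separate matter. For 1.62 to give 80% power at n = 20, the SD of the difference must be about 2.45. Both readings are carried forward.

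**Precision.** With women's orders balanced, the expected sample variance of the differences becomes SD² + k² × (number of women)/(n − 1). For 10 women, p = 1.2 and change scores: √(2.45² + 2.4² × 10/19) = √(6.00 + 3.03) = 3.01, against 2.45.

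Simulated power, two-sided 5%, n = 20, 10 women, true difference 1.62, SD of the difference held at 2.45 for both outcomes:

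| p | paired t, end values | paired t, change scores | sex-by-period model, change scores |
|---|---|---|---|
| 0 | 80% | 80% | 79-80% |
| 0.4 | 80% | 78% | 80% |
| 0.8 | 78% | 73% | 79% |
| 1.2 | 76% | 65% | 80% |

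The mean estimate stays at about 1.62. Under the null, paired t rejection on change scores at p = 1.2 falls to 1.8%: the test becomes conservative, not anti-conservative. A period term without sex-by-period recovers only to 72% at p = 1.2, because the men carry no phase shift.

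With the stated SD of 1.0 and 10 women, end-value power stays at about 100%. On change scores with the variance doubled (SD √2 = 1.41), it goes from 99.8% to about 95% at p = 1.2.

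**The case against.** **The effect and the cycle length are assumed.** The documents give no phase effect on clamp values, no number of women and no cycle length. This stands: every size above is conditional. At p = 0.4 the loss is at most about 2 points.

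**Phase biases the diet comparison.** A reader might infer this, but the documents do not support it. Order is randomised in blocks within gender, so phase is aliased with period, not with diet. Only chance imbalance in women's orders among completers shifts the estimate, and by little.

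**Every woman is tested in opposite phases, follicular to luteal in period 1.** This is also tempting and too strong. It is exact only near 28 days. The direction depends on which visit is the anchor: the OGTT at visit 2 is listed among the metabolic measures and precedes the baseline IVGTT and clamp, so it could be the first testing day. The 42-day shift remains under any anchor.

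**Power collapses.** Taking SD 1.0 and solving for the difference that gives 80% power at n = 20 yields 0.66 mg/kg/min. At that effect, losses to 57% or lower can be produced. But the plan's difference is 1.62, and 0.66 is only about 8% of 8.1.

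**Part of the remedy is planned, and the article is condensed.** Data Analysis does mention diet order, period effects and an expanded diet-and-period model, and the abstract mentions ANOVA. However, the stated diet comparison is the paired t test, and nothing separates phase in women from period in men. Figure 1 is not shown, and visit windows may sit in the full protocol. The phase rule and the spacing are nevertheless both fixed in the text, and they do not fit together for typical cycles.

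**Conclusion.** The point holds as a moderate design weakness. The phase rule covers only the start of testing, and the stated spacing leaves matching tests 42 days apart. For women with cycles near 28 days, that puts the two post-diet clamps in different phases and partly aliases phase with period. Reading the rule as the first test day of each period does not help, since a fixed 4-week washout does not deliver it for typical cycles.

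The diet estimate remains unbiased in expectation. The cost is precision: with 10 women and p of 0.4 to 1.2, power is about 80-76% on end values and 78-65% on change scores if the SD of the difference is 2.45. With the stated SD of 1.0 the loss is negligible on end values and small on change scores. A 6:4 order split would shift the estimate by about 0.08 (end values) or 0.16 mg/kg/min (change scores) at a 10% phase effect.

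**What to change.** Reconcile the follicular-phase statements in Screening and Metabolic Measures with the diet and washout timing in the abstract and Overview, so that each woman's matching tests in the two periods fall in the same cycle phase. State which testing days the rule covers, and record cycle day at every test.

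For the primary insulin sensitivity analysis, replace the unadjusted paired t test with a model that includes period and sex-by-period terms. Sex is already the randomisation stratum.

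The cost is flexible booking, slightly longer participation for some women, one extra data field and two degrees of freedom. In the simulation the two extra terms cost less than 1 percentage point of power when there is no phase effect.

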##### Oral Glucose Tolerance Test (OGTT)

Participants will ingest 75 g of glucose over 2 minutes. Blood samples will be drawn at 0 and 120 minutes to analyze plasma glucose levels and to determine diabetes status (WHO 1999 criteria).

##### Intravenous Glucose Tolerance Test (IVGTT)

Using IVGTT, acute insulin secretory response will be measured. First, baseline blood will be collected at -10 and 0 minutes, after which 50 ml of 50% glucose will be delivered intravenously over a 3-minute period. Blood will then be collected for measurement of insulin at the 3, 4, 5, 6, 8, 10, 15, 20, 25, and 30 minute time points. The early insulin secretory response will be calculated as the mean incremental plasma insulin level from the 3rd to the 5th minute after the glucose bolus.

##### Hyperinsulinemic Euglycemic Clamp

A euglycemic glucose clamp will be used to measure insulin sensitivity. After collecting baseline blood and plasma glucose levels at 0 minutes, the clamp will be initiated by an intravenous bolus injection of insulin (9 mU/kg). Insulin will then be constantly infused at a rate of 40 mU/m2/min for approximately 120 minute into an arm vein, whilst glucose is variably infused to maintain euglycemia. Plasma glucose values will be monitored every 5 minutes during the clamp while the variable infusion rate of glucose is adjusted to maintain blood glucose at a constant concentration of 5 mmol/L for the last 40 minutes of the clamp.

Plasma glucose concentrations will be measured by the glucose oxidase method (ELM 105 Radiometer). Plasma insulin levels will be measured by chemiluminescent microparticle immunoassay and plasma high sensitivity CRP will be determined by immunotubimetric assay (Abbott Archicentre ci162000).

#### Measurement of Advanced Glycation End Products (AGEs) and Their Receptors

The concentrations of AGE- (CML, CEL, and MG-H1) modified proteins in serum and free AGEs in urine will be quantified using UPLC MSMS as previously described [24]. AGE-modified proteins will also assayed [25] in urine (neat) using an indirect ELISA as previously described [26].

The pool of sRAGE (circulating RAGE from proteolytic cleavage and AGER gene transcription; RnD Systems) and endogenous secretory RAGE (esRAGE) (circulating RAGE from AGER1 gene transcription only) will be analyzed in plasma by ELISA according to the manufacturer’s instructions.

#### Cardiovascular Measures

##### Blood Pressure

Resting systolic and diastolic blood pressure and pulse rate will be measured using an automated oscillometric measurement system (Omron) after a 30 minute rest. The mean blood pressure derived from 3 measurements will be recorded.

##### Lipid Profile

Lipid profile-related parameters to be measured include plasma total cholesterol, triglycerides, and low density lipoprotein (LDL) and high density lipoprotein (HDL) cholesterol using a standard commercial enzymatic assay (Beckman Coulter LX20PRO Analyzer and Synchron) and Systems Lipid and Multi Calibrators (Beckman Coulter Diagnostics).

#### Inflammatory Markers

##### Cytokines and Chemokines

Plasma inflammatory markers (IL-1ß, -6, -8 and -10, TNFα, MIF, and MCP-1) will be measured using a commercial automated chemiluminescent enzyme immuno assay (EIA) and immulite analyzer (Diagnostic Products Corporation), while plasma CRP will be analyzed using highly sensitive near infrared particle immunoassay rate methodology and a Beckman Coulter Synchron LX system Chemistry Analyzer (Beckman Coulter Inc).

##### Nuclear Factor-κB (NF-κB) Activity

Nuclear extracts of white blood cells will be obtained and analyzed for the binding capacity of the p50/p65 subunit of NF-κB to an NF-κB oligonucleotide consensus sequence as per the manufacturer’s instructions (Active Motif, CA, USA).

